**Methods:**

This study will include 120 patients (60 per group, aged 20–80 years) with 1- or 2-level lumbar spinal stenosis, who will be recruited from six hospitals. The study will be conducted from July 2021 to December 2024. The primary outcome (Oswestry Disability Index at 12 months after surgery) will be evaluated through a modified intention-to-treat method. The secondary outcomes will include the following: visual analog scale score for low back and lower extremity radiating pain, EuroQol 5-dimensions score, surgery satisfaction, walking time, postoperative return to daily life period, postoperative surgical scars, and some surgery-related variables. Radiographic outcomes will be analyzed using magnetic resonance imaging or computed tomography. All outcomes will be evaluated before the surgery and at 2 weeks, 3 months, 6 months, and 12 months postoperatively. This protocol adheres to the Standard Protocol Items: Recommendations for Interventional Trials (SPIRIT) guidelines for reporting of clinical trial protocols.

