### Outcome measures

#### Primary outcome

The primary outcome will be the difference in Oswestry Disability Index (ODI) scores between baseline and at 1 year after surgery [14]. Among the wide range of patient-reported outcomes, the ODI is the most suitable for functional evaluation of the lumbar spine. Patients are instructed to provide an answer of 0–5 for each section in the ODI questionnaire, with a score of 5 representing the greatest disability. The total score is calculated as a percentage of the total maximum score (excluding questions with no responses). In cases where a patient provides two or more responses to a single question, the highest score will be counted.

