#### Secondary outcomes

##### Clinical outcomes

Visual analog scale (VAS) score for low back pain and radiating pain of the lower extremities: scores range from 0 to 10; a higher score indicates more severe painPatient’s quality of life, as assessed by the EuroQol 5-dimensions questionnaire (EQ-5D): EQ-5D contains five questions with five responses for each question, and the total score is converted into the final EQ-5D value, ranging from 0.000 to 1.000; higher score indicates a better quality of life [15].Surgery satisfactionWalking timePostoperative return to daily life periodSurgical scars, as evaluated using the Patient and Observer Scar Assessment Scale 2.0, which contains six parameters with 10-point scoring system; 6 represents normal skin and 60 represents the worst scar imaginableSurgery-related variables, such as postoperative drainage (mL), operation time (minutes), admission duration (hours), and postoperative creatine kinase (International Unit/L)

Patient-reported outcomes will be collected from the participants at baseline and at 2 weeks, 3 months, 6 months, and 12 months after surgery.

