#### Sample size and statistical analysis

This trial will recruit 120 participants (60 participants per group) to confirm the primary outcome equivalence between biportal endoscopic and conventional decompressive laminectomy. Previous studies have indicated a minimal clinically important ODI difference of 12.8 [17], as well as a standard deviation of 18.8, at 1 year after endoscopic decompressive laminectomy [18]. A required sample size of 60 patients per group was determined based on these values and the following parameters: alpha of .05, power of .90, two-sided confidence interval of 95%, and a 20% loss to follow-up.

All statistical analyses will be performed using SPSS 26.0 (version 26.0, Chicago, IL, USA). A *P* value < .05 will be considered significant. A modified intention-to-treat (mITT) analysis will be used. The mITT strategy indicates that participants are analyzed on whether they underwent a randomly assigned surgery (to avoid the effects of crossover and dropout, which may disrupt the random assignment to the treatment groups). Participants who do not complete the follow-up schedule will be excluded from the analysis, and there will be no additional enrollment.

In each group, changes in secondary outcomes from baseline to follow-up will be analyzed with repeated measures analysis of variance. Differences in other clinical and radiologic outcomes, as well as adverse events, between the two groups will be analyzed using Student’s t-test (for continuous variables) and chi-square test (for categorical variables).

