## Discussion

The aim of this multicenter, prospective RCT is to compare the efficacy and safety of biportal endoscopic decompressive laminectomy with those of conventional microscopic decompressive laminectomy in patients with LSS. While endoscopic spine surgery, in particular, the biportal endoscopic technique, has become an increasingly used approach in this patient group, it is not without certain challenges.

Previous studies have suggested that a sufficient level of experience is essential for performing biportal endoscopic surgery in patients with lumbar stenosis. Biportal endoscopic decompressive laminectomy has a particularly steep learning curve, as competency in this technique requires the completion of approximately 58 cases [19]. Indeed, a previous study reported that complications occurred in 7 (10.3%) of 68 cases during this learning curve [20]. Therefore, under the premise that conventional spine surgery requires skill, a learning curve of approximately 60 cases is considered necessary for the biportal endoscopic technique.

Nevertheless, previous studies have indicated that the clinical outcomes achieved with the biportal endoscopic technique are similar to those of open microscopic surgery when the learning curve is completed; the biportal endoscopic technique has also been shown to yield superior early postoperative outcomes [10, 18, 21]. According to a recent meta-analysis of 383 patients from five studies, the majority of postoperative clinical outcomes are equivalent between biportal endoscopic laminectomy and conventional microscopic laminectomy [11]. However, the biportal endoscopic technique has been shown to have additional advantages, such as less immediate postoperative back pain, a shorter length of hospital stay, earlier ambulation, a reduced need for opioids, and lower postoperative segmental instability [21–23].

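### The primary 12-month ODI comparison drops patients with incomplete follow-up and ignores their earlier ODI scores; one longitudinal model over all scheduled visits would use them at no extra data cost

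*Protocol article*

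**What the plan says.** All references are to the protocol article.

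- **Primary outcome.** The Primary outcome section says: "The primary outcome will be the difference in Oswestry Disability Index (ODI) scores between baseline and at 1 year after surgery". The abstract agrees on scale and time point: "The primary outcome (Oswestry Disability Index at 12 months after surgery) will be evaluated through a modified intention-to-treat method".
- **When ODI is measured.** Table 1 (evaluation schedule) marks ODI at screening and at 2, 12, 24 and 52 weeks. The Clinical outcomes section says "Patient-reported outcomes will be collected from the participants at baseline and at 2 weeks, 3 months, 6 months, and 12 months after surgery", and the abstract says "All outcomes will be evaluated before the surgery and at 2 weeks, 3 months, 6 months, and 12 months postoperatively".
- **Secondary outcomes.** Neither the abstract's list nor the list under Clinical outcomes includes ODI.
- **Analysis.** In Sample size and statistical analysis, the only longitudinal method is confined to secondary outcomes and to changes within an arm: "In each group, changes in secondary outcomes from baseline to follow-up will be analyzed with repeated measures analysis of variance". Between arms: "Differences in other clinical and radiologic outcomes, as well as adverse events, between the two groups will be analyzed using Student’s t-test" (chi-square for categorical variables), with no time points given.
- **Incomplete follow-up.** The same section states that patients whose follow-up is not completed are left out of the analysis and not replaced. It plans for 20% loss to follow-up.

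**The concern.** The trial measures its primary scale four times after surgery, and its stated handling of missing data makes no use of three of those measurements. A patient with ODI at 2 weeks, 3 months and 6 months but not at 12 months is removed, although those scores carry information on the missing value.

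Two things are at stake. The first is precision: the 12-month comparison rests on about 48 patients per arm when 60 were randomized and many of the missing 12 will have been seen earlier. The second is the missing-data assumption. A completers-only comparison is safe when loss to follow-up is unrelated to outcome. If patients who are doing badly at 3 or 6 months are more likely to leave, and more so in one arm, the completers' difference can be biased. A likelihood-based model of all visits allows loss to depend on the ODI scores already observed, which is a weaker assumption. The article gives nothing from which to size that second effect, so only precision is calculated below.

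**Working it through.** **Inputs from the article (Sample size and statistical analysis):** 60 per arm, 20% loss, SD 18.8 at 1 year, ODI difference 12.8, two-sided alpha 0.05, power 0.90.

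**Inputs assumed:** correlation rho between 6- and 12-month ODI of 0.6 to 0.8, and the share of lost patients who have a 6-month score. The article gives neither.

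**Step 1: the plan's own figure.** n = 2 × 18.8² × (1.960 + 1.282)² / 12.8² = 45.3, so 46 per arm. Then 46 / 0.8 = 57.5, so 58, close to the stated 60. The point disputes no part of this figure. Whether this formula suits an equivalence aim is a separate question.

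**Step 2: what is discarded.** Expected completers: 60 × 0.8 = 48 per arm. Lost: 12 per arm, 24 in all. If each had all three early visits, 24 × 3 = 72 early ODI scores would be dropped.

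**Step 3: variance of a 12-month arm mean.** Let m be the number per arm with a 6-month score, 48 of whom also have a 12-month score.

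- Completers only: σ²/48.
- Using the 6-month score: σ² × [(1 − rho²)/48 + rho²/m].
- Ratio of the second to the first: 1 − rho² × (1 − 48/m).

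With m = 60 (every lost patient seen at 6 months) the ratio is 1 − 0.2 × rho². With m = 54 (half of them) it is 1 − 0.111 × rho². With m = 48 there is no gain from the 6-month visit.

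| rho | ratio, m = 60 | effective n per arm (48 / ratio) | ratio, m = 54 |
|---|---|---|---|
| 0.6 | 0.928 | 51.7 | 0.960 |
| 0.7 | 0.902 | 53.2 | 0.946 |
| 0.8 | 0.872 | 55.0 | 0.929 |

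The variance falls by 7 to 13% in the best case, and by 4 to 7% if half the lost patients have a 6-month score.

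**Step 4: in ODI points.** With SD 18.8 and 48 completers per arm, the 95% CI half-width is 1.96 × 18.8 × √(2/48) = 7.5 points. Multiplying by √0.928 and √0.872 gives 7.2 and 7.0 points. The best-case gain is about 0.3 to 0.5 points of half-width.

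**Step 5: baseline.** The table uses the raw correlation. When baseline ODI is in the model, the relevant figure is the 6-to-12-month correlation given baseline. It is not in the article and is usually lower, so the share saved by the earlier visits would be smaller.

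**Step 6: multiplicity of the earlier contrasts.** Three further tests at 0.05 each, if independent, give a family-wise error of 1 − 0.95³ = 14%. With the 12-month test included it is 1 − 0.95⁴ = 19%.

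**The case against.** The strongest reply is that this is a condensed article, that a single primary time point with other scheduled visits is ordinary design, and that the role of intermediate visits is commonly set out in a statistical analysis plan. That stands for the naming gap: the absence of ODI from the secondary list would be no more than a missing detail. It does not answer the exclusion rule, which the article itself fixes and which settles how incomplete patients are handled.

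A second reply is that the variance gain is a best case on correlations nobody has stated. That also stands, and the figures are given as upper limits for that reason.

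Three stronger readings are tempting, and the article does not support them.

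- A reader might infer that early ODI goes untested. The between-arm t-test for other clinical outcomes names no time points and could cover it. An early ODI comparison is neither named nor excluded.
- A reader might infer that the trial expects an early ODI difference, because the Discussion says "the biportal endoscopic technique has also been shown to yield superior early postoperative outcomes". That sentence summarizes previous studies. The specific advantages listed there are back pain, hospital stay, ambulation, opioid need and segmental instability, not ODI. The trial's own hypothesis is similarity.
- A reader might infer that nothing pre-specified can be said on early recovery. Pain VAS, EQ-5D, walking time and return to daily life are named secondary outcomes scheduled from 2 weeks, and admission duration is named too.

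**Conclusion.** The point holds as an avoidable loss of information in the primary analysis. The plan measures ODI at every visit and then, by its own rule, discards the earlier scores of patients without a 12-month value.

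The size is modest: at most about a 7 to 13% reduction in the variance of the 12-month arm mean, or 52 to 55 effective patients per arm instead of 48. This assumes 20% loss, a 6-month score for all lost patients and rho of 0.6 to 0.8. It shrinks with baseline adjustment and with fewer 6-month scores. The weaker missing-data assumption is a further benefit that cannot be sized from the article.

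The stated sample size is unaffected, and the point does not show that the primary conclusion would be wrong. It is worth acting on because the better method needs nothing that is not already scheduled.

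**What to change.** Replace the completers-only rule for the primary analysis with one longitudinal model fitted to all scheduled postoperative ODI scores. Its terms are arm by visit and baseline ODI by visit, with an unstructured covariance across visits. Keep every patient who has any postoperative ODI.

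- **Primary:** the between-arm difference at 12 months with its 95% CI. With baseline as a covariate, the contrast is the same whether the outcome is written as the 12-month score or as the change from baseline, so the abstract and the Primary outcome section need not be treated as different analyses.
- **Secondary or exploratory:** the 2-week, 3-month and 6-month differences with 95% CIs from the same model, labelled as such and without a confirmatory claim because of multiplicity.
- **Sensitivity:** the completers-only comparison can stay as a supporting analysis.

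The cost is wording in the protocol and the analysis plan. No new patients, visits or questionnaires are needed.

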#### Secondary outcomes

##### Clinical outcomes

Visual analog scale (VAS) score for low back pain and radiating pain of the lower extremities: scores range from 0 to 10; a higher score indicates more severe painPatient’s quality of life, as assessed by the EuroQol 5-dimensions questionnaire (EQ-5D): EQ-5D contains five questions with five responses for each question, and the total score is converted into the final EQ-5D value, ranging from 0.000 to 1.000; higher score indicates a better quality of life [15].Surgery satisfactionWalking timePostoperative return to daily life periodSurgical scars, as evaluated using the Patient and Observer Scar Assessment Scale 2.0, which contains six parameters with 10-point scoring system; 6 represents normal skin and 60 represents the worst scar imaginableSurgery-related variables, such as postoperative drainage (mL), operation time (minutes), admission duration (hours), and postoperative creatine kinase (International Unit/L)

Patient-reported outcomes will be collected from the participants at baseline and at 2 weeks, 3 months, 6 months, and 12 months after surgery.

##### Radiographic outcomes

The degree of central canal release and canal dimension, as measured using postoperative magnetic resonance imaging (MRI) or computed tomographyOther radiographic complications, as assessed using simple radiographs during the follow-up period

Baseline radiographs in the anteroposterior, lateral, flexion, and extension views will be used to score spondylolisthesis and segmental instability at the surgery level. A preoperative spine MRI will be systematically checked, and the severity of the canal compromise will be evaluated based on Schizas classification [16].

Safety will be assessed by evaluating all adverse and severe adverse events; all incidents will be reported to the appropriate institution, as required. All outcomes will be recorded by the blinded assessor in the eCRF system (Table 1).

**Table 1 Tab1:** Evaluation schedule

Visit type	Screening	Operation	Follow-up			
Visit	1	2	3	4	5	6
Visit week	-4–0 weeks	0–2 days	2 weeks	12 weeks	24 weeks	52 weeks
			± 5 days	± 4 weeks	± 8 weeks	± 8 weeks
Informed consent	O					
Demographics^a^	O					
Inclusion/exclusion	O					
Randomization		O				
Operation		O				
MRI (or CT)^b^	O	O				
Simple radiographs	O		O	O	O	O
ODI	O		O	O	O	O
EuroQol 5-dimensions	O		O	O	O	O
VAS	O		O	O	O	O
POSAS				O	O	O
Other surveys^c^			O	O	O	O
Adverse events		O	O	O	O	O

*MRI* magnetic resonance imaging; *CT* computed tomography; *ODI* Oswestry Disability Index; *VAS* visual analog scale for low back pain and radiating pain of the lower extremities; *POSAS* Patient and Observer Scar Assessment Scale

^a^Baseline patient characteristics, including past medical/surgical history, physical examination, and laboratory tests

^b^A CT scan will be obtained if MRI cannot be performed

^c^ Including surgery satisfaction, walking time, and postoperative return to daily life period

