### Operation technique

#### Case group: biportal endoscopy

The most critical aspect of the biportal endoscopic technique is that the procedure proceeds by securing a working space through two portals. Each portal is approximately 1 cm in size; one portal serves as the viewing portal, and the other serves as the working portal. The portals are positioned immediately lateral to the spinous process and separated by 1–1.5 cm. When operating on the patient’s left side, the viewing portal is positioned on the cranial side; the working portal is positioned on the caudal side and is within the interlaminar space. Using a Cobb elevator, the paraspinal muscle is detached from the spinous process and lamina to secure a working space. Subsequent laminectomy and flavectomy procedures are performed using the ULBD technique (Fig. 2) [5]. During the surgical procedure, continuous irrigation is performed through the viewing portal, with the pressure being adjusted to 30–40 mmHg.

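### Canal release and dimension rest on one scan at 0–2 days with no stated common measure with baseline; read both scans alike and adjust the comparison for the preoperative value

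*Protocol article*

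**What the plan says.** In the protocol article, Radiographic outcomes defines the outcome as "The degree of central canal release and canal dimension, as measured using postoperative magnetic resonance imaging (MRI" or computed tomography. For the preoperative MRI, the same section says that "the severity of the canal compromise will be evaluated based on Schizas classification". It names no grade or unit for the postoperative reading.

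Table 1 (Evaluation schedule) marks MRI (or CT) at Visit 1 (screening, −4 to 0 weeks) and Visit 2 (operation, 0–2 days), and at none of Visits 3 to 6. Simple radiographs are marked at all four of those visits. A footnote to the MRI row states: "A CT scan will be obtained if MRI cannot be performed".

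The Methods part of the abstract says: "All outcomes will be evaluated before the surgery and at 2 weeks, 3 months, 6 months, and 12 months postoperatively".

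Sample size and statistical analysis gives two rules. Within each group, "changes in secondary outcomes from baseline to follow-up will be analyzed with repeated measures analysis of variance". Between groups, the rule is that "Differences in other clinical and radiologic outcomes, as well as adverse events, between the two groups will be analyzed using Student’s t-test". That test applies where the variable is continuous; categorical outcomes get a chi-square test. No adjustment for a preoperative value is mentioned.

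The description of the biportal technique adds that, during surgery, "continuous irrigation is performed through the viewing portal, with the pressure being adjusted to 30–40 mmHg". The description of conventional surgery mentions no irrigation.

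**The concern.** Three features of this outcome limit what it can show.

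- **Timing.** The only postoperative canal image is taken within two days of surgery. It describes the canal immediately after the operation and cannot describe the canal at the time of the 12-month ODI. So early an image may show fluid as well as the bone and ligament removed. One technique uses continuous irrigation and none is described for the other, so the amount of fluid may differ by arm. Randomization would not remove such a difference, because it would be a consequence of the surgery.
- **Measure.** Degree of release is naturally a comparison with the preoperative canal, but the article does not say that the two scans are read on the same measure.
- **Test.** A preoperative scan is scheduled for every patient, yet the stated between-arm test ignores it and so gives up precision that would cost little to gain.

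At stake is how well the trial can show on imaging that a unilateral-approach endoscopic technique and a bilateral laminectomy decompress the canal to a similar degree. This is one secondary outcome; the primary analysis is not involved.

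**Working it through.** The article gives no figure for this outcome to reproduce, so most of the check sets its statements side by side.

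**1. Schedule.** MRI (or CT) has two marks in Table 1. The screening mark is preoperative, so the operation-visit mark (0–2 days) must be the postoperative scan. The 12-month visit is at 52 ± 8 weeks, that is 52 − 8 = 44 to 52 + 8 = 60 weeks. The canal measurement thus comes about 44 to 60 weeks before the primary endpoint, with no later canal image. Because simple radiographs are marked at Visits 3 to 6, the blanks in the MRI row look deliberate. The abstract's schedule for all outcomes and Table 1 cannot both be right for this outcome; Table 1 is the more specific.

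**2. Measures named.**

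| Time | Named in the article | Not stated |
|---|---|---|
| Preoperative | Schizas grade | Whether canal dimension is also read |
| Postoperative | Degree of release, canal dimension | Whether the Schizas grade is repeated |

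No measure is named at both times. Both scans are planned, so a common measure can be read from them.

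**3. Analysis.** A t-test or chi-square test on the postoperative reading is valid in a randomized comparison without any baseline. It is less precise than it could be. If the within-group repeated-measures analysis is meant to cover this outcome, which the wording leaves open, it needs the same measure at both times.

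**4. What adjustment could gain.** With pre–post correlation ρ, the large-sample variance of the adjusted arm difference, relative to the unadjusted comparison of postoperative values, is 1 − ρ². The article does not give ρ, so these values are assumptions:

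- ρ = 0.3: 1 − 0.09 = 0.91 (9% less variance)
- ρ = 0.5: 1 − 0.25 = 0.75 (25% less)
- ρ = 0.7: 1 − 0.49 = 0.51 (49% of the variance removed, 51% left)

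At ρ = 0 there is no gain, and the cost is one degree of freedom. A plain change score is not a substitute. With equal variances its relative variance is 2(1 − ρ), which is 1.4, 1.0 and 0.6 at the same three values, so it never beats adjustment here and is worse than no adjustment when ρ is below 0.5.

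**5. What cannot be computed.** The article gives neither the size or direction of any early-fluid effect nor the share of patients who will have CT.

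**The case against.** The strongest reply is that an early scan is a coherent way to record what the operation achieved, before later changes and before the 20% loss to follow-up that the sample size allows for. The article nowhere claims that the scan describes the canal at 12 months. This stands: the timing is a design choice that calls for a label, and there is no ground to require a later scan. Moving the scan would answer a different question.

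Four stronger readings are tempting, and the article does not support them:

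- **That the postoperative scale differs from baseline.** No postoperative scale is named. Silence is not a difference, and a journal article may leave reading rules to the full protocol.
- **That a like-for-like change is impossible.** Images are planned at both times, so a common measure is available. The between-arm comparison does not need a change score in any case.
- **That MRI and CT are mixed by design.** CT is a fallback, under one footnote covering both scans. A patient who cannot have MRI may have CT twice. A switch within a patient is possible but not planned, and nothing suggests imbalance between arms.
- **That early fluid biases the comparison.** The irrigation described is intraoperative, drainage is an outcome in both arms, and nothing is said about retained fluid at imaging. Fluid is a reasonable inference and no more than a possibility.

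The abstract mismatch is also minor. Its statement about all outcomes cannot literally cover operation time or drainage either, and the section on clinical outcomes correctly limits that schedule to patient-reported measures. Correcting it is clerical.

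**Conclusion.** The point holds as a small improvement to one secondary outcome. Three statements follow from the article: the only postoperative canal scan falls at 0–2 days, no measure is named at both times, and the between-arm test makes no use of the preoperative scan. The outcome therefore supports an immediate postoperative statement only, and a cheap gain in precision is left unused. The size of that gain depends on a correlation the article does not give; the values in the working are illustrative. The possible contribution of early fluid remains unquantified and should be reported as a limitation, not as a demonstrated bias. Should the full protocol already specify common readings and an adjusted analysis, only the label and the abstract wording remain to be changed. The primary ODI analysis and the sample size do not depend on any of this.

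**What to change.** 1. Read the preoperative and postoperative scans on the same measures: canal dimension and Schizas grade at the index level. Because one- and two-level surgery are both eligible, state in advance which level counts for two-level patients.
2. Compare arms on the postoperative value adjusted for the preoperative value: ANCOVA for dimension and ordinal regression for the grade, in place of the plain t-test or chi-square.
3. Keep CT patients in the main analysis, so that no randomized patient is dropped because of modality. Add a sensitivity analysis limited to patients with MRI at both times.
4. Label the outcome *immediate postoperative*, and note early fluid as a possible contributor.
5. Reword the abstract so that its assessment schedule agrees with Table 1.

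The cost is extra reading of images already scheduled. Counting one level per patient and assuming that neither missing reading is already planned, this is one added preoperative dimension and one added postoperative grade for each of 120 patients: at most 120 × 2 = 240 readings. No scan is added or moved, and the primary analysis does not change.
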